### Study aims

Guided by CST and social networks research, the ENGAGED study will evaluate the feasibility and efficacy of a technology-supported weight loss program for obese adults. Specifically, the primary aim of the ENGAGED study is to conduct a three-group randomized controlled trial testing the efficacy of the ENGAGED technology-supported behavioral weight loss program, as compared to the same program delivered using standard paper and pencil self-monitoring, and self-guided behavioral weight loss supported by participants receiving DVD’s depicting DPP treatment. Primary outcomes include: (1) weight loss and (2) behavioral adherence, which is operationalized by (a) self-monitoring of diet and activity and (b) attainment of diet and activity goals. As a secondary outcome, the time spent administering the intervention by lifestyle coaches will also be examined to assess intervention costs. The second aim of the ENGAGED study is to test whether the weight loss in the technology-supported condition is mediated by behavioral adherence to self-monitoring and achievement of diet and activity goals.

We hypothesize that using a theory-guided, technology-supported weight loss treatment will result in clinically significant weight loss with fewer in-person sessions by preserving regular social support, accountability, and feedback via mobile technology. Further, we hypothesize that technology-supported weight loss treatment will result in greater weight loss compared to the traditional paper self-monitoring approach.

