### Randomization

Eligible participants will be scheduled for a group time and assigned to a team with seven other participants, all of whom will be randomized to the same condition. Group randomization will be completed by a statistician, and neither participants, nor coaches, will find out group assignment until the first group session. The intervention timeline is presented in Figure
2.

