In addition to in-person group sessions, STND participants will receive individual coaching calls. Coaching calls will be scheduled on a weekly basis during the initial eight weeks of the study and monthly during months 3–6. Coaches will review submitted Keeping Track diaries and determine the participant’s level of achievement for each goal using standardized adherence criteria for the study. Coaching calls will last approximately 10–15 minutes and follow a structured script aiming to reinforce success and problem solve around barriers to change. Four content areas will be covered during each call: (1) weight loss, (2) adherence to dietary and physical activity self-monitoring, (3) attainment of diet and activity goals, and (4) goal setting.

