### Treatment fidelity

Fidelity checklists will be prepared for group and telephone coaching sessions. Checklists for each session will specify a) good counseling practices; b) prescribed session content; and c) proscribed session content. Coaches will undergo training to become familiarized with the modified DPP protocol and to role-play potential conflicts and situations that may arise during group and telephone sessions. Study staff will also attend weekly clinical meetings to discuss any participant conflicts that may arise. All group and telephone coaching sessions will be audio recorded, and each month a random sample of 10% of the recordings will be coded by study staff to evaluate treatment fidelity. If fidelity falls below 90% on any of the fidelity checks, staff will be retrained.

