#### Coaching time

Coaches will monitor the number of minutes preparing for and conducting individual coaching calls throughout the first 6 months of the intervention.

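### Call minutes for the secondary coaching-time outcome come from coaches who know the arm, although every call is already audio recorded and could be timed from the recording

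*Protocol article*

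**What the plan says.** - **Role of the measure.** Study aims: "As a secondary outcome, the time spent administering the intervention by lifestyle coaches will also be examined to assess intervention costs".
- **Source of the minutes.** Outcome measures, Coaching time: "Coaches will monitor the number of minutes preparing for and conducting individual coaching calls throughout the first 6 months of the intervention". The outcome is therefore preparation plus call time for individual calls.
- **Blinding.** Randomization: "neither participants, nor coaches, will find out group assignment until the first group session". After that session the coaches know the arm. The two arms also use visibly different tools, paper diaries in STND and the smartphone application in TECH.
- **Recordings.** Treatment fidelity: "All group and telephone coaching sessions will be audio recorded". The only stated use is that "each month a random sample of 10% of the recordings will be coded by study staff to evaluate treatment fidelity".
- **Calls.** The STND section gives the frequency, "Coaching calls will be scheduled on a weekly basis during the initial eight weeks of the study and monthly during months 3–6", and the length, "Coaching calls will last approximately 10–15 minutes and follow a structured script". The TECH section says that arm also receives regular coaching calls. SELF receives none, so coaching time can be compared only between TECH and STND.

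**The concern.** The people who deliver the programme being costed also supply the measurement, and they do so knowing the arm. Logging by recall or by rounding need not be even across arms. A coach who works from an automatic data summary may judge or round a call differently from one who works through a paper diary. Short scripted calls do not protect the comparison, because a true arm difference in call length is then likely to be only a few minutes, which is also the scale of ordinary rounding.

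At stake is whether a TECH v STND difference in call minutes, or the lack of one, reflects time used or logging habits. The trial already produces a record of call length that does not depend on the coach's view of the arm, and the article does not assign it to this purpose.

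**Working it through.** The article gives no standard deviation, effect size or power for coaching time, so there is no planned figure to reproduce. The check has three parts.

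**1. Premises side by side.** Study aims names coaching time as a secondary outcome. Coaching time puts the recording of minutes in the coaches' hands. Randomization ends their masking at the first group session. Treatment fidelity records all telephone sessions and states no timing use. These statements are compatible, so there is no contradiction. The point is the choice of data source for one component.

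**2. Size of the call component.** Inputs are from the STND section; that TECH follows the same schedule is assumed.
- Calls per participant: 8 weekly + 4 monthly (months 3, 4, 5, 6) = 12.
- Scheduled call time: 12 × 10 = 120 to 12 × 15 = 180 minutes; midpoint 150.

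**3. Illustration of differential logging.** The per-call error is an assumption with no basis in the documents. Shift per participant = 12 × error per call.

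| Assumed arm difference in logging, min per call | Shift per participant, min | Share of 180 to 120 call min | Share of 150 min |
|---|---|---|---|
| 1 | 12 | 7–10% | 8% |
| 2 | 24 | 13–20% | 16% |
| 3 | 36 | 20–30% | 24% |

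The denominator is call time only. Preparation belongs to the outcome but has no stated length, so the share of total coaching time would be smaller by an unknown amount.

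To see whether such a shift could mislead a test, take 32 per arm (Sample size and power), no true difference, two-sided alpha 0.05 (assumed), independent participants (assumed) and a between-participant SD of 20, 30 or 40 minutes (assumed). The standard error is SD × √(2/32) = SD × 0.25, that is 5, 7.5 or 10 minutes. The probability of declaring a difference in the direction of the bias is about Φ(bias/SE − 1.96).

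| Bias, min | SD 20 | SD 30 | SD 40 |
|---|---|---|---|
| 12 | Φ(2.40 − 1.96) = 0.67 | Φ(1.60 − 1.96) = 0.36 | Φ(1.20 − 1.96) = 0.22 |
| 24 | Φ(4.80 − 1.96) = 1.00 | Φ(3.20 − 1.96) = 0.89 | Φ(2.40 − 1.96) = 0.67 |

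These figures show only that a small uneven error per call, summed over 12 calls, can matter at this sample size. They do not estimate what will happen.

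**The case against.** The case against is substantial.

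- **A condensed article.** The Coaching time section is one sentence. It does not say whether minutes come from a timer, a phone record or an estimate, and it does not rule out a check against recordings. This stands in part: the article does name the coaches as the source, but the full protocol may already hold the check.
- **Preparation is untouched.** A reader might infer that the recordings would measure the arm difference in coaching time exactly. They would not. The outcome includes preparation, which is never recorded and where the arms differ most visibly by design: manual diary review in STND, automatic summaries in TECH. This stands in full and limits the point to call minutes.
- **No evidence of differential logging.** Rounding alone biases the comparison only if it works differently by arm. The documents suggest neither a size nor a direction. A reader might take 8–24% as the expected error; it is an illustration from an assumed 1–3 minutes per call.
- **Modest consequence.** The Data analytic plan does not list coaching time among the between-group comparisons, the hypotheses concern weight loss, and both arms attend the same eight group sessions. If true differences in call length are small, call minutes alone can hardly carry a cost conclusion. This stands and keeps the severity low.
- **Feasibility.** The recording format, the retention period and who starts and stops the recording are not stated, and unanswered call attempts would leave no recording. This stands as a practical caveat; the coach log covers the gaps.

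What the objections leave intact is that unblinded coach-recorded minutes are the only stated source for a component that the trial already captures independently of the coach's log.

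**Conclusion.** The point holds as a low-severity improvement limited to call minutes. Differential logging by coaches who know the arm could bias that part of the TECH v STND comparison, by an amount and in a direction the documents do not give. Each assumed minute of uneven logging per call would amount to 12 minutes per participant against 120–180 scheduled call minutes.

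The conclusion rests on three readings: that monitoring by coaches means they record their own time, that TECH follows the STND call schedule, and that the full protocol does not already provide for timing from the recordings. It does not extend to preparation time, to which activities count as coaching time, or to the primary outcomes of weight loss and behavioral adherence.

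**What to change.** In the Coaching time section:

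1. Take call minutes from the duration of the audio recordings already required under Treatment fidelity, with the coach log as fallback where a recording is missing or failed.
2. Keep coach logs for preparation time.
3. Report call minutes and preparation minutes separately by arm, so that readers see how much of any difference rests on self-report.
4. Compare logged with recorded call minutes by arm. Agreement that is similar in both arms would lend indirect support to the preparation logs; a gap in one arm would be a warning about them.

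The cost is staff time to read recording durations and link them to participants and calls. It adds no participant burden and no new recording procedure, provided the recordings or their durations are retained. The remaining weakness is that preparation time and missing recordings still depend on the logs.

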### Data analytic plan

#### Linear mixed modeling

Data will be analyzed on an intent-to-treat basis. The basic modeling approach will entail linear mixed models for longitudinal data. The primary aim is to test for treatment group differences on weight loss at 3-, 6-, and 12-months as well as differences in behavioral adherence and goal attainment at 3- and 6-months. Linear mixed models do not require that participants are measured at all time points, and therefore can include participants with missing data across time. In these analyses, we will examine changes across time by treating time as a nominal variable in the analysis to allow for non-linear trends. In addition to the effect of time, the main independent variable is treatment groups, a between-subjects factor with 3 levels: STND, TECH and SELF. A priori Helmert contrasts
[38] will be used to test the following comparisons at 3- and 6-months: 1) STND and TECH vs. SELF and 2) TECH vs. STND. We will also examine group by time interactions to test whether change in outcome across time differs by group.

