### Eligibility

A total of 96 participants who meet the inclusion and exclusion criteria listed in Table
1 will be recruited in two cohorts. Participants will be between 18–60 years old with a body mass index (BMI) between 30–40 kg/m^2^, weight stable for the past 6 months, not currently enrolled in a formal weight loss program or taking weight loss medications, and be willing to self-monitor and wear an accelerometer daily for 6 months. Participants will be excluded if they have any unstable medical conditions, are currently pregnant, or taking any medications known to influence weight. See Table
1 for a complete list of exclusion criteria.

**Table 1 T1:** ENGAGED inclusion and exclusion criteria

**Inclusion**	**criteria**
	• BMI 30.0-39.9 kg/m^2^
	• 18-60 years old
	• Interested in losing weight through diet and physical activity changes
	• Weight stable over the past 6 months
	• Not receiving concurrent weight loss treatment
	• Willing to self-monitor (on smartphone or paper) and wear an accelerometer daily for 6 months
	• Able to attend all assessments and group sessions
	• Have or be willing to learn basic technology usage skills
**Exclusion**	**criteria**
	• Has one or more of the following unstable medical conditions: uncontrolled hypertension or diabetes, angina pectoris, myocardial infarction, plantar fasciitis, transient ischemic attack, cancer undergoing active treatment, or cerebrovascular accident within the past 6 months
	• Has insulin-dependent diabetes, Crohn’s Disease, obstructive sleep apnea requiring use of a CPAP, plantar fasciitis
	• Requires use of an assistive device for mobility
	• Has been hospitalized for a psychiatric disorder in the past 5 years
	• Contraindications for moderate intensity physical activity
	• Currently taking any weight-loss medications or committed to following an incompatible dietary regimen
	• Currently pregnant, trying to get pregnant, or lactating
	• Current bulimia nervosa or binge eating disorder
	• Current substance or alcohol or dependence
	• Current attention deficit hyperactivity disorder or major depressive disorder
	• Currently taking medication(s) known to cause weight gain (i.e. Prednisone, Depakote, Diebeta, Diabinese, Cardura, Inderal, Zyprexa)
	• Expresses active suicidal ideation

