#### Physical activity adherence

Physical activity will be objectively measured by an accelerometer (Actigraph #7164, Pensacola, FL) over 7 days at baseline, 3-, and 6-months. The accelerometer will be attached to an elastic belt and worn on the right hip. Minutes of moderate-to-vigorous intensity physical activity will be measured in a modified bout lasting a minimum of eight consecutive minutes. Adherence will be ascertained on the basis of how well the participant’s bout-corrected accelerometer count corresponds to the weekly activity goal.

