#### Dietary intake adherence

We measure adherence to calorie goals at 3 and 6 months using 3 day 24 hour recalls. Using pilot data from a previous trial, we observed a standard deviation of change in calories of 498 at month 3 and 431 at month 6, with a correlation of 0.9 between the two time points. With 80% power and an n=30 in both groups, we will be able to detect a calorie reduction difference of 375 calories.

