#### Physical activity adherence

Physical activity adherence is measured by accelerometer at months 3 and 6 as the number of minutes of moderate to vigorous intensity physical activity per week. Using data from a previous trial
[39], we assume a standard deviation of 142 minutes/week at months 3 and 6, with a correlation of 0.9 between the two time points. With 80% power and an n=30 in both groups, we will be able to detect a 100 minute/week difference between the two groups.

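### The stated repeated-measures model gives change-score or raw-level contrasts and makes inefficient use of the baseline values; adjusting for baseline would sharpen mainly the activity comparison

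*Protocol article*

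**What the plan says.** The Linear mixed modeling section sets out the approach: "The basic modeling approach will entail linear mixed models for longitudinal data". Time is nominal, and the section continues: "In addition to the effect of time, the main independent variable is treatment groups", the three arms being the levels of that factor. It adds: "We will also examine group by time interactions to test whether change in outcome across time differs by group". The Helmert contrasts (STND and TECH against SELF, then TECH against STND) are placed at months 3 and 6. The Study design section defines time as a four-level factor whose first level is baseline. No baseline covariate is named.

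The baseline values exist. Weight is measured and dietary recalls are taken at baseline, and the accelerometer is worn "over 7 days at baseline, 3-, and 6-months".

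The power section uses baseline differently from one outcome to the next:
- **Activity** is sized on follow-up levels: "we assume a standard deviation of 142 minutes/week at months 3 and 6".
- **Calories** are sized on change: "standard deviation of change in calories of 498 at month 3", and 431 at month 6.
- **Weight** is sized on loss, with SDs of 8.4 and 10.7 lb.

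**The concern.** When baseline is an outcome level and the group-by-time terms are unconstrained, the model can deliver two kinds of contrast. The interaction compares change from baseline between arms. A contrast at month 3 or 6 on the outcome itself compares follow-up levels and ignores baseline. Under the usual assumptions neither has a smaller variance than the comparison adjusted for baseline. The raw level discards the baseline information, and the change score subtracts the baseline with a fixed weight of one, whatever the actual correlation.

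At stake is precision on outcomes that the Study aims section calls primary, since attainment of diet and activity goals is among them. With about 30 analysed per arm, precision is scarce: the planned detectable activity difference of 100 min/week is 57% of the full 175 min/week goal (100/175).

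**Working it through.** **Inputs from the article.** n = 30 per arm and 80% power. Activity: SD 142 at both visits, correlation 0.9. Calories (change): SDs 498 and 431, correlation 0.9. Weight loss: SDs 8.4 and 10.7 lb, correlation 0.86. Alpha is not stated; two-sided 0.05 is assumed.

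**Reproducing the stated figures.** The SD of the mean of months 3 and 6 is 0.5 × √(s3² + s6² + 2·r·s3·s6). The detectable difference is (1.96 + 0.84) × SD × √(2/30).

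| Outcome | SD of two-visit mean | Detectable | Stated |
|---|---|---|---|
| Activity, min/week | 138.4 | 100.1 | 100 |
| Weight loss, lb | 9.21 | 6.67 | 6.6 |
| Calories, kcal | 452.8 | 327.5 | 375 |

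Activity and weight reproduce with no covariate adjustment, so the activity figure rests on follow-up levels alone. The calorie figure does not reproduce, but it errs on the cautious side and is a separate matter; only the relative gain is used below.

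**Activity: adjusted against raw level.** The residual SD is SD × √(1 − r²), where r is the assumed correlation of baseline with the two-visit mean.
- r = 0.3: 100.1 × √0.91 = 95.5 min/week; power at 100 min/week about 84%.
- r = 0.5: 100.1 × √0.75 = 86.7 min/week; power about 90%.
- r = 0.7: 100.1 × √0.51 = 71.5 min/week; power about 98%.

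If the interaction (change score) were used for activity instead, and the baseline SD equalled that of the two-visit mean, the factor would be √(2(1 − r)). That gives 100.1 × √1.4 = 118.4 at r = 0.3 and 100.1 × √0.6 = 77.5 at r = 0.7. The change score is worse than the raw level below r = 0.5 and better above it. The adjusted analysis is better than both across this range.

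**Calories: adjusted against change score.** With equal baseline and follow-up SDs (assumed), the detectable difference is multiplied by √((1 + r)/2).
- r = 0.3: √0.65 = 0.806, so 19% smaller (327.5 to 264 kcal).
- r = 0.7: √0.85 = 0.922, so 8% smaller (327.5 to 302 kcal).

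**Weight loss.** Here the outcome is already a change, so the relevant quantity is the correlation c of baseline weight with loss, and the factor is √(1 − c²). For c = 0 the detectable difference is 6.67 lb; for c = 0.3 it is 6.67 × √0.91 = 6.36 lb. The gain is 0% to 5%.

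**Cohort.** For two equal cohorts whose means differ by d SDs, a cohort term removes a share (d²/4)/(1 + d²/4) of the variance. At an assumed d = 0.3 that is 0.0225/1.0225 = 2.2%, moving the weight figure from 6.67 to 6.59 lb.

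**The case against.** The strongest reply is that a journal article need not list covariates. The text speaks of a basic approach and a main independent variable, and neither phrase is exhaustive. That stands as far as it goes: silence about covariates is not a fault. But the article does fix a structure, with baseline as a level of time plus group and group by time. The point is that a better structure is available for the same data.

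A reader might infer more than the document supports:
- **That baseline is left out altogether.** It is not. Weight is analysed as loss, calories are sized as change, and baseline is a level of time. What remains is a choice between valid analyses of differing precision.
- **That raw body weight is contrasted, with a far larger SD.** The outcome is weight loss, and the SDs of 8.4 and 10.7 lb are those of loss.
- **That chance imbalance biases the contrasts.** Under randomization it adds variance. An observed imbalance shifts a particular estimate, but the estimator is not biased by it.
- **That the trial falls short of its stated power.** The stated figures assume no adjustment.
- **That cohort must be in the model** because participants "will be recruited in two cohorts". The expected gain is negligible.

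It can also be said that the activity power paragraph supplies an SD and specifies no model, and that the outcome section judges activity against the weekly goal. That is fair, so the activity gain applies to minutes per week, the scale on which the trial is sized. Finally, all the gains treat participants as independent, whereas teams of eight share one allocation (96/8 = 12 teams, four per arm). The absolute figures may therefore overstate precision with or without adjustment.

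**Conclusion.** The point holds as a matter of efficiency. The stated model yields change-score or raw-level contrasts, and the baseline data already being collected would support more precise ones. The gain is material for activity (detectable difference 5% to 29% smaller, from about 100 to between 95.5 and 71.5 min/week), moderate for calories (19% to 8% smaller than with the change score) and small for weight loss (0% to 5%). These sizes rest on assumed correlations of 0.3 to 0.7 (0 to 0.3 between baseline weight and loss), on equal SDs for calories, on two-sided alpha of 0.05 and on independent participants. The document gives none of the baseline correlations, so the gain cannot be fixed more closely.

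**What to change.** In the Linear mixed modeling section, state that the post-baseline values of weight, calorie and fat intake, and activity minutes are analysed with the baseline value of the same outcome and its interaction with time as covariates. To the same end, keep baseline as a time level and constrain the arms to a common baseline mean. State that the Helmert contrasts are taken from this model. For the dietary recalls the change serves TECH versus STND only, because SELF has no recalls at months 3 and 6. The self-monitoring ratios have no baseline value of their own and stay as they are. A cohort term is optional.

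The cost is a change of wording and, for the covariate version, one slope per follow-up visit: two parameters for activity and diet, three for weight. No new data are needed. Settling this in advance also removes any later choice between level, change and adjusted analyses.
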